#### Summary Statistics of the Dataset

Our contracted Intermountain Healthcare data analyst will execute Oracle database SQL queries to extract a deidentified version of the dataset, encrypt it, and transfer it securely to a password-protected and encrypted computer on which we will perform secondary analyses. Intermountain Healthcare uses dedicated tables to track changes in diagnosis and procedure codes over time. The dataset contains information on patient encounters over the past 11 years. For the last 5 years, data captured for children cover more than 400 pediatric primary care physicians, 360,698 pediatric patients (age zero to 17 years), and 1,557,713 clinical encounters per year. Data captured for adults cover more than 600 primary care physicians, 878,448 adult patients (age ≥18 years), and 5,786,414 clinical encounters per year. Asthma prevalence is approximately 7.6% in the Intermountain Healthcare pediatric population and approximately 8.6% in the Intermountain Healthcare adult population. The dataset includes approximately 400 attributes and represents electronic documentation of approximately 85% of pediatric care and approximately 60% of adult care delivered in Utah [33,52]. Intermountain Healthcare dedicates extensive resources to data accuracy and integrity. Due to its large size and attribute richness, the dataset gives us many advantages for exploring the proposed predictive models.

In addition, we will use 21 environmental variables recorded over 11 years by regional monitoring stations within the geographic area covered by Intermountain Healthcare. These variables include particulate matter up to 2.5 μm in size (PM_2.5_) and 10 μm in size (PM_10_), carbon monoxide (CO), nitrogen dioxide (NO_2_), sulfur dioxide (SO_2_), ozone (O_3_), temperature, relative humidity, wind speed, precipitation, dew point, and activities of viruses (adenovirus; enterovirus; human metapneumovirus; influenza A virus; influenza B virus; parainfluenza virus types 1, 2, and 3; rhinovirus; and respiratory syncytial virus). Because the monitoring stations are spread across a large geographic area including the entire state of Utah, the readings of the same environmental variable can differ greatly at different monitoring stations at any time.

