### Aim 3: Develop an Algorithm to Compute Optimal Thresholds for Risk Strata

In risk-stratified management, chronic disease patients are stratified into multiple levels [14,15]. This aim will compute the optimal thresholds for these levels that minimize total future cost of all patients factoring in the management programs’ costs. Total future cost implicitly reflects patient health outcomes, health care use, efficiency of care, and the management programs’ benefits. For instance, fewer hospitalizations usually lead to lower costs. The following discussion focuses on stratification based on predicted patient risk of experiencing a specific type of undesirable event (eg, hospitalization or emergency department visit). The case of stratification based on predicted cost or with more than one type of undesirable event can be handled similarly. Our discussion applies to any predictive model and is based on a fixed period in the future, such as the next 12 months.

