#### Threshold Computation Algorithm

We will conduct quantitative analysis to determine the optimal management level for each risk percentile. We will proceed through the risk percentiles one by one, from the highest to the lowest. Given a risk percentile, we will compute for each management level the average future cost per patient in the percentile if patients in the percentile are put into the level. The level with capacity remaining in its management program and the lowest average future cost per patient will be chosen for the risk percentile.

More specifically, consider a risk percentile and an average patient whose predicted risk falls into the percentile. If the patient is enrolled in a management program, we estimate that the patient’s future cost will change by delta = the program’s cost – the program’s benefit gained by reducing undesirable events=*c*
_
*i*
_–*avg_n*
_
*e*
_**p***c*
_
*e*
_ compared with no enrollment. Here, *c*
_
*i*
_ is the program’s average cost per patient. Factors such as increased medication cost due to better medication adherence are included in *c*
_
*i*
_. *avg_n*
_
*e*
_ is the average number of undesirable events that a patient in the risk percentile will experience in the future. *p* is the percentage of undesirable events the management program can help avoid, reflecting the program’s benefit. *c*
_
*e*
_ is the average cost of experiencing the undesirable event once. *c*
_
*i*
_ and *p* can be obtained from statistics reported in the literature for the management program [39,88]. *avg_n*
_
*e*
_ can be obtained by making predictions on historical data and checking the corresponding statistics for the risk percentile. *c*
_
*e*
_ is obtained from statistics on historical data. The management level with the smallest delta is optimal for the risk percentile. If no statistics on *c*
_
*i*
_ and *p* of a management program are available in the literature, the clinician in our research team ([name]) will provide rough estimates based on experience. We will perform sensitivity analysis when choosing thresholds by varying the estimated values of *c*
_
*i*
_ and *p* to obtain the full spectrum of possible outcomes in Aim 4.

The preceding method performs an exhaustive search among all management levels for each risk percentile. In practice, we would expect *avg_n*
_
*e*

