_ to decrease as the predicted patient risk of experiencing undesirable events becomes smaller. We will investigate using this property to reduce the search space when going through the risk percentiles one by one, from the highest to the lowest.

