#### Outcome Evaluation and Sample Size Justification

We will compare outcomes achieved by 2 predictive models using the best machine learning algorithm. The first model will use patient, physician profile, and environmental variable features; the second only patient and environmental variable features. We will test 3 hypotheses: adding physician profile features will be associated with reduced (1) costs, (2) hospital admissions, and (3) emergency department visits. We will test each hypothesis twice, once for children and once for adults. Cost data will be log-transformed due to skewed distribution [13]. We will accept the primary hypothesis if the first model can reduce the log cost by 10% multiplied by its standard deviation compared with the second model. One-sided paired-sample *t* test will be used to test the difference in log cost between the 2 models’ outcomes. McNemar’s test will be used to test the difference in hospital admissions and emergency department visits. At a significance level of .05, a sample size of 857 instances has 90% power to confirm the primary hypothesis. The 11th year’s data include approximately 27,000 children and 75,000 adults with asthma, providing adequate power for testing the primary hypothesis.

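### The threshold algorithm takes event averages from single risk percentiles without using the expected monotonicity or their sampling error, so with one year of data levels can fall out of risk order and cut-offs can shift by a few percentiles, usually at small cost

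*Protocol article*

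**What the plan says.** Aim 3 sets out to "compute the optimal thresholds for these levels that minimize total future cost of all patients", counting programme costs. Under Threshold Computation Algorithm, percentiles are handled one at a time from the highest risk down. For each level the plan computes delta = c_i − `avg_n_e` × p × c_e (programme cost, events, share avoided, cost per event). The choice rule is: "The level with capacity remaining in its management program and the lowest average future cost per patient will be chosen for the risk percentile". The event average "can be obtained by making predictions on historical data and checking the corresponding statistics for the risk percentile".

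The section closes by expecting `avg_n_e` "to decrease as the predicted patient risk of experiencing undesirable events becomes smaller". The only use proposed for this is: "We will investigate using this property to reduce the search space". On uncertainty it says: "We will perform sensitivity analysis when choosing thresholds by varying the estimated values of" c_i and p. It does not mention varying `avg_n_e`.

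Under Aim 4 (Estimate Outcomes), thresholds are computed for the 11th year's data, which hold "approximately 27,000 children and 75,000 adults with asthma".

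**The concern.** A threshold exists only if the assigned levels are ordered by risk. Nothing in the choice rule ensures this. Each percentile is decided on its own raw mean, and over most of the risk range neighbouring percentiles have nearly equal true means. Sampling error can then push one percentile below a break-even point and the next, lower-risk one above it.

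The plan already holds the information that would stabilise the estimate, namely the expected fall of `avg_n_e` with risk, but does not use it for estimation. The sensitivity analysis treats `avg_n_e` as known. At stake are the cut-offs that Aim 3 delivers and that Aim 4 compares with heuristic ones.

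**Working it through.** **1. Cohort size.** The article says: "Asthma prevalence is approximately 7.6% in the Intermountain Healthcare pediatric population and approximately 8.6% in the Intermountain Healthcare adult population". With its patient counts, 360,698 × 0.076 = 27,413 children and 878,448 × 0.086 = 75,547 adults. Both are within 3% of the stated 27,000 and 75,000.

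**2. Patients per percentile** (100 percentiles assumed). One year: 27,000/100 = 270 and 75,000/100 = 750. If historical data means ten pooled years of similar size: 2,700 and 7,500.

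**3. Why order depends on `avg_n_e`.** Levels a and b have equal delta where `avg_n_e` = (c_a − c_b) / [c_e × (p_a − p_b)]. Before capacity limits, the chosen level therefore depends only on which side of such points the estimated `avg_n_e` falls. A decreasing estimate gives ordered levels; a raw estimate that reverses across a break-even does not.

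**4. Signal against noise.** Assumed example: mean 0.1 events per patient-year, AUC 0.7, Poisson counts.
- Near the 91st percentile, neighbouring true means are 0.201 and 0.193, a gap of 0.008. The standard error of the difference is √[(0.201 + 0.193)/270] = 0.038 for children and √[(0.201 + 0.193)/750] = 0.023 for adults. The chance of a reversal is 0.41 and 0.36.
- At the very top, the means are 0.564 and 0.382, a gap of 0.182 against √[(0.564 + 0.382)/270] = 0.059. The chance of a reversal is 0.001.

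Reversals therefore belong to the flatter part of the curve, not to the extreme top.

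**5. How often levels are unordered with raw means.** The documents give no event rate, no c_e, and no c_i or p for the lower levels, so two sets of assumptions were simulated.
- *Setting A:* AUC 0.70 or 0.75, 8% of patients with an event, 1.3 events per case, Poisson counts, break-evens at the top 3%, 10% and 30%, no capacity limit.
- *Setting B:* 56 scenarios with mean events 0.03 to 0.2, c_e $2,000 to $15,000, AUC 0.7 or 0.8, assumed c_i and p for the lower levels, and event variance = mean + mean². Medians over scenarios are shown.

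| Per percentile | A | B, no caps | B, 3% cap on case management | B, caps 1%/5%/20% on upper three levels |
|---|---|---|---|---|
| 270 | about 100% | 81% | 81% | 26% |
| 750 | 95–99% | 49% | 51% | 7% |
| 2,700 | 68–83% | 17% | 21% | 0% |
| 7,500 | 37–60% | 3% | 3% | 0% |

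In B without caps, single scenarios run from 0% to 100% at both one-year sizes.

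**6. Size of the error, and what a decreasing isotonic fit does** (setting B, no caps, medians):

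| Per percentile | Misassigned percentiles of 100, raw → isotonic | Excess cost, % of achievable net saving, raw → isotonic |
|---|---|---|
| 270 | 2.4 → 1.3 | 1.5 → 0.65 |
| 750 | 1.45 → 0.98 | 0.57 → 0.24 |
| 2,700 | 0.76 → 0.64 | 0.14 → 0.09 |
| 7,500 | 0.48 → 0.45 | 0.04 → 0.03 |

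The worst B scenarios with raw means lose 29% at 270 and 10% at 750. In A, misassigned percentiles fall from 8–11 to 4–5 for children and from 5–7 to 3–4 for adults. Over three cut-offs, 8 to 11 is about 3 to 4 per cut-off. The one-year loss in A is about 1% to 5% of the achievable gain. Isotonic fitting cuts the loss by 69–75% at 270 and 57–65% at 750. In B it left no unordered levels in any scenario.

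**7. The search shortcut as a remedy.** Read as never moving back up a level, it restores order. It recovers little of the loss: 5.1% falls to 4.9% of the achievable gain in A at 270, AUC 0.70.

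**8. If monotonicity fails.** In an assumed example with the top three percentiles set too low, the isotonic fit loses 1.3% against 0.8% for raw means at 750 per percentile, and 1.2% against 0.04% at 7,500. With a monotone truth it was still worse than raw means in up to 6% (A) or about 9% (B) of single runs. With the 1%/5%/20% caps it was worse on average in 1 of 56 scenarios at 270 and 3 of 56 at 2,700.

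**The case against.** The strongest case against is that this is a refinement with little cost attached.

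- **Errors near a break-even are cheap**, because the competing levels have almost equal delta there. This stands, and is why the median loss is small.
- **The rule respects capacity**, and the introduction puts case management at 1% to 3% of patients. A cap on that level alone changes little; tight caps on all upper levels make disorder uncommon. This stands in part.
- **Historical data may mean several years.** The article does not fix this. With pooled years disorder is less common.
- **The search shortcut could itself enforce order.** It could, but the authors only undertake to investigate it, and it leaves the cut-offs resting on noisy means.
- **Other uncertainty is larger and already varied.** For enrolment against none, break-even is c_i/(p × c_e), so moving p from 30% to 40% multiplies it by 0.30/0.40 = 0.75, a 25% shift. At an assumed 0.25 events, Poisson error of a percentile mean is √(0.25/270)/0.25 = 12%, or √(0.25/750)/0.25 = 7%. That ranks the uncertainties; it does not justify omitting one. Clinicians also make the final placement, which softens the consequence.
- **A condensed article may leave smoothing and intervals to a fuller plan.** For interval detail this is fair. But the article does state where `avg_n_e` comes from and what monotonicity is for, and that stated choice is what is questioned.

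A reader might infer that the algorithm will usually fail to give thresholds, and that a monotone fit cures this at no cost. The documents support neither. The frequency depends on event rates, costs and capacities they do not give; misplacement is only reduced; and the benefit depends on a monotonicity the authors expect but have not shown.

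**Conclusion.** The point holds in a limited form. The stated method estimates `avg_n_e` percentile by percentile, does not ensure ordered levels, and leaves sampling error in `avg_n_e` out of the threshold sensitivity analysis.

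With one year of data and no tight capacities, unordered levels are likely for children (median 81% in B, about 100% in A) and about even to likely for adults (49% and 95–99%). They are less common with pooled years or binding capacities. Cut-offs are typically off by a few percentiles. The loss is usually about 0.5% to 5% of the achievable saving, with some scenarios well above that.

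All frequencies and losses rest on assumed event rates, costs, effects and risk curves; only the patient counts come from the article. The finding does not invalidate Aim 3 or Aim 4. It identifies a better estimator from the same data, provided the true curve is close to monotone.

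**What to change.** Under Threshold Computation Algorithm:

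1. Estimate `avg_n_e` by an isotonic regression, or a smooth monotone Poisson regression, of event count on risk percentile, and compute delta from the fitted values.
2. Compare the fit with the raw percentile means and report where they disagree, since a truly non-monotone curve would make the fit worse than the raw means.
3. Add uncertainty in `avg_n_e` to the sensitivity analysis already planned for c_i and p, as bootstrap intervals for each cut-off.
4. State which years supply `avg_n_e`. Pooling years makes the problem smaller.

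This takes a few sentences and standard routines on data already in hand. It guarantees ordered levels before capacity limits apply and reduces misplacement without removing it. The price is reliance on monotonicity, which step 2 checks.

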#### Performance Evaluation

The threshold computation algorithm will be evaluated in Aim 4.

### Aim 4: Conduct Simulations to Estimate Outcomes of Risk-Stratified Patient Management for Various Configurations

To determine a predictive model’s value for future deployment in clinical practice, we need to estimate outcomes of risk-stratified patient management when the model is used and determine how to generalize the model to differing sites collecting different sets of attributes. Our models will be built on Intermountain Healthcare datasets. Our simulations will guide how to deploy the models in another health care system. No previous study has either estimated outcomes for a model with more than one management strategy or determined the attributes most important for generalizing the model. We will demonstrate our simulation method for the task of risk-stratified management of (1) asthmatic children and (2) asthmatic adults by using our models for predicting acute care use for asthma in the following year (see Aim 1a: Definition of Asthma Cases and Outcomes), the hierarchy of risk-stratified management levels shown in Figure 1, and our algorithms described in Aims 2 and 3. Our simulation method is general and can be used to deploy other models in clinical practice. We will first evaluate the technique in Aim 1.

#### Outcomes

We will focus on the outcomes of costs, hospital admissions, and emergency department visits in the following year. Cost is the primary outcome, reflecting health care use and efficiency of care. Other outcomes are secondary and are indirectly reflected in costs.

#### Estimate Outcomes

Given a set of attributes and a predictive model, we will estimate each outcome. We will use the same method as in Aim 1 to train the model on the first 10 years’ data. For the 11th year’s data, we will obtain prediction results, compute thresholds for risk strata, then estimate the outcome in a way similar to Aim 3. For example, consider a patient who will have a cost of *h* and experience *n*
_
*e*
_ undesirable events in the following year with no program enrollment. If the patient is enrolled in a management program, we estimate that the patient’s future cost will become *h* + *c*
_
*i*
_–*n*
_
*e*
_**p***c*
_
*e*
_, where *c*
_
*i*
_, *p*, and *c*
_
*e*
_ are as defined in Aim 3. The overall outcome estimate is the aggregate of estimated outcomes for all patients. Using a similar approach, we can identify the minimum accuracy requirement of the model for it to be clinically valuable.

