## Introduction

### Risk-Stratified Management of Chronic Disease Patients

Chronic diseases affect approximately 52% of Americans and consume 86% of health care costs [1]. Example management strategies for care include case management, disease management, supported self-care, and wellness promotion (listed in Table 1 in descending order of intensity). Each strategy is widely used and has its own benefits and properties [2,3]; for example, most major employers purchase and nearly all private health plans offer case management services [2,4] targeting early interventions at high-risk patients to prevent large expenditures and avoid deterioration of health status. Proper use of case management can reduce hospital admissions and readmissions and emergency department visits by up to 30% to 40% [3,5-9], lower costs by up to 15% [6-10], and improve patient satisfaction, quality of life, and treatment adherence by 30% to 60% [5]. A case management program can cost more than US $5000 per patient per year [6] and typically enrolls only 1% to 3% of targeted patients due to resource limitations [11]. For maximal benefit, only patients expected to incur the highest costs and/or those with the poorest prognoses should be enrolled.

**Table 1 table1:** Description of patient management strategies.

Management strategy	Description
Case management	“A collaborative process that assesses, plans, implements, coordinates, monitors, and evaluates the options and services required to meet [a patient’s] health and human service needs” [12]. It involves a case manager who calls the patient periodically, helps make doctor appointments, and arranges for health and health-related services.
Disease management	Example intervention: check electronic medical records to find and call high-risk patients with the disease who require a specific test, but have not had it for ≥2 years.
Supported self-care	Example intervention: give patients electronic monitoring tools for self-management.
Wellness promotion	Example intervention: mail educational materials on how to maintain health.

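### Cut-offs are recomputed for each model, so where capacity does not bind, the secondary admission and emergency-visit comparisons in Aim 4 can mix better ranking with a different program size

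*Protocol article*

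**What the plan says.** Aim 4, Estimate Outcomes, works model by model: "Given a set of attributes and a predictive model, we will estimate each outcome". On the 11th year's data the order is "we will obtain prediction results, compute thresholds for risk strata, then estimate the outcome in a way similar to Aim 3".

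The Aim 3 rule that this refers to has a cost objective, to "minimize total future cost of all patients factoring in the management programs’ costs". It goes through the risk percentiles from the highest down: "The level with capacity remaining in its management program and the lowest average future cost per patient will be chosen for the risk percentile". The average number of undesirable events per percentile, which drives that choice, "can be obtained by making predictions on historical data and checking the corresponding statistics for the risk percentile". It therefore changes with the model.

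Under Outcome Evaluation and Sample Size Justification, the models with and without physician profile features are compared. The hypotheses are that "adding physician profile features will be associated with reduced (1) costs, (2) hospital admissions, and (3) emergency department visits". Cost is primary and the other two outcomes are secondary. McNemar's test is named for admissions and emergency visits. The article does not say that both models use the same cut-offs or the same numbers per level. It gives no capacity figure for Aim 4. The Introduction says only, as background, that a case management program "typically enrolls only 1% to 3% of targeted patients due to resource limitations".

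**The concern.** The comparison is meant to show what the added features contribute, since the threshold algorithm has its own separate analysis in the same section. Yet with cut-offs set by cost, the features can also change how many patients are enrolled. Avoided events equal p times the events occurring among enrolled patients, so they rise with enrollment as well as with ranking.

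In the cost outcome a larger program is paid for, because each enrollee adds c_i. In the admission and emergency-visit outcomes it is free. A reduction under hypotheses (2) or (3) may therefore be partly bought by more enrollment, and a smaller program can hide part of a real gain in ranking. The same ambiguity would carry into the planned table of estimated outcomes by attribute combination, which other health systems are meant to use when deciding which attributes to collect.

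**Working it through.** **The plan's own figure.** The only sample size in this section is 857, for the primary log-cost hypothesis. One-sided, α = 0.05, power 90%, effect 0.1 SD: ((1.645 + 1.282)/0.1)² ≈ 857. It reproduces and is not in question.

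**Break-even.** A percentile is worth enrolling when c_i − avg_n_e·p·c_e < 0, that is, when avg_n_e > c_i/(p·c_e). The article gives no values for c_i, p or c_e in Aim 4, so the following are assumptions:
- c_i $20, p 10%, c_e $4,000: 20/(0.10 × 4,000) = 0.05 events.
- c_i $400, p 25%, c_e $4,000: 400/(0.25 × 4,000) = 0.4 events.

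**Model (assumed).** One program, no cap, lognormal event rates with mean 0.10 and log SD σ = 1.5. The score correlates ρ with the log rate. Solving for the AUC of any event in the year gives ρ = 0.540 (AUC 0.70, without physician features) and ρ = 0.835 (AUC 0.80, with them). The 0.1 difference matches the one used in the Aim 1a sample size.

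The share of all events captured by the top fraction q is f(q) = Φ(ρσ + Φ⁻¹(q)), with ρσ = 0.810 and 1.253. The mean rate in a percentile is 0.10 × 100 × [f(q) − f(q − 0.01)], and it is enrolled if that exceeds break-even. Each pair below is without versus with physician features.

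| Break-even | Enrolled | Captured, own cut-offs | Captured at equal enrollment |
|---|---|---|---|
| 0.05 | 67% vs 47% | 89.4% vs 88.1% | at 47%: 76.9% vs 88.1%; at 67%: 89.4% vs 95.5% |
| 0.075 | 48% vs 35% | 77.6% vs 80.7% | at 35%: 66.5% vs 80.7%; at 48%: 77.6% vs 88.5% |
| 0.15 | 18% vs 17% | 45.8% vs 61.7% | at 17%: 44.3% vs 61.7%; at 18%: 45.8% vs 63.2% |
| 0.20 | 10% vs 12% | 31.9% vs 53.1% | at 10%: 31.9% vs 48.9%; at 12%: 35.8% vs 53.1% |
| 0.40 | 2% vs 4% | 10.7% vs 30.9% | at 2%: 10.7% vs 21.2%; at 4%: 17.4% vs 30.9% |

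**High break-even (0.4).** The gain is 30.9 − 10.7 = 20.2 points. The part due to enrollment is (30.9 − 21.2)/20.2 = 48% if both are held at 2%, or (17.4 − 10.7)/20.2 = 33% if both are held at 4%.

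**Low break-even (0.05).** With 27,000 children, 2,700 events and p = 10%, avoided events are 270 × 0.894 = 241 versus 270 × 0.881 = 238. The better model avoids about 1% fewer. At equal 47% enrollment the figures are 270 × 0.769 = 208 versus 238.

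**Second model (assumed).** Binormal score, AUC 0.70 versus 0.80, mean rate 10%, p = 0.30, 27,000 patients:
- Break-even 0.5 times the mean, no cap: 76% vs 55% enrolled, 744 vs 720 events averted. Net saving is nevertheless 436 vs 497 in units of c_e, so cost still favors the better model.
- Break-even 0.75 times the mean, no cap: 639 vs 650 averted; the reversal is gone.
- Break-even 2 times the mean, no cap: 9% vs 14% enrolled, 194 vs 381 averted, a gap of 187. With both at 10% it is 209 vs 311, a gap of 102.
- Cap 3%, break-even up to 2 times the mean: both enroll 3%, 82 vs 133 averted.
- Cap 3%, break-even 4 times the mean: 1% vs 3% enrolled, so a cap equalizes only when it binds in both models.

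**The case against.** The best defense concerns the estimand. Aim 4 sets out to estimate what happens once a model is in use, and a better model legitimately changes how many patients are worth enrolling. Recomputed cut-offs belong to that effect, and discrimination is already tested by AUC in Aim 1. This stands: the model-specific run is not an error and should not be replaced. It does not, however, tell a reader how much of an event reduction comes from ranking and how much from a larger program.

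The capacity rule also stands as a limit. Where capacity binds in both models, enrollment is equal and ranking decides the result. The 1% to 3% figure makes that plausible for case management. It is background on that strategy alone, though, and Table 1 lists three less intensive ones.

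The planned sensitivity analysis over c_i and p would show dependence on the break-even ratio, but it does not equalize enrollment. The illustration uses one program, whereas Aim 4 has a hierarchy (Figure 1 is not shown), so shifts between levels were not modelled.

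A reader might infer that the two models must enroll different numbers, that the more accurate model will tend to look worse, or that the cost ratio and not accuracy decides the sign. The documents do not support this. Different enrollment is conditional on capacity. In these checks the reversal was about 1% to 3% of averted events and appeared only for an uncapped program at roughly half the mean event rate or less. From break-even 0.075 upward, every tabulated value favors the better model. Nor is the primary cost result distorted in this way, because it charges c_i per enrollee.

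**Conclusion.** The concern holds in a limited form. As described, nothing equalizes enrollment between the two models, so where capacity does not bind, hypotheses (2) and (3) can mix ranking with program size. The more consequential direction is a high break-even, where the better model enrolls more and the apparent benefit is enlarged: about one third to one half of the gain at break-even 0.4 in the lognormal example. The reversal at low break-even is small.

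These sizes rest on assumed event rates, costs, AUCs and a single uncapped program, none of which the article fixes. Only two secondary outcomes are involved, and the remedy is a cheap addition to the plan.

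**What to change.** Keep the run with model-specific cut-offs as the estimate of outcomes in use. For hypotheses (2) and (3), add a run in which both models place the same number of patients at each level. This can be done at the stated capacities, or at each model's cut-offs in turn so that neither model is favored. For every run, report the number enrolled and the program cost per level. Attribute event reductions to physician features only as far as they persist at equal enrollment.

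The cost is a few extra simulation runs per population and a short addition to the text. The drawback is that common cut-offs are not cost-optimal for both models, which is why the model-specific run stays beside them.
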